## Abstract

Nutrition is an important determinant of health. At present, nutrition programs in India mainly emphasize improving maternal and child nutrition. Adult nutrition has not received due attention, though diseases like hypertension and diabetes are largely preventable through changes in dietary and physical activity behaviour. Little is known about the best approaches to improve dietary behaviours, especially the role of modern information technology (IT) in health education. We describe the protocol of the SMART Eating (Small, Measurable and Achievable dietary changes by Reducing fat, sugar and salt consumption and Trying different fruits and vegetables) health promotion intervention. A Cluster Randomised Controlled Trial will evaluate the effect of an IT-enabled intervention on nutrition behaviour among urban adults of Chandigarh, India. Formative research using a qualitative exploratory approach was undertaken to inform the intervention. The IT-enabled intervention programme includes website development, Short Message Service (SMS), e-mail reminders and interactive help by mobile and landline phones. The IT-enabled intervention will be compared to the traditional nutrition education program of distributing pamphlets in the control group. The primary outcome will be the percentage of study participants meeting the dietary intake guidelines of the National Institute of Nutrition, Hyderabad, India and the change in intake of fat, sugar, salt, fruit and vegetables after the intervention. The difference in differences method will be used to determine the net change in dietary intakes resulting from the interventions. Measurements will be made at baseline and at 6 months post-intervention, using a food frequency questionnaire. The formative research led to the development of a comprehensive intervention, focusing on five dietary components and using multi-channel communication approach including the use of IT to target urban North Indians from diverse socio-economic backgrounds. The Cluster Randomised Controlled Trial design is suitable for evaluating the effectiveness of this IT-enabled intervention for dietary behaviour change.

## Background

Diet is one of the important social determinants of health. Over a period of time, due to industrialisation and urbanisation, diets have changed. Dietary intakes of fat, sugar, salt, or fruit and vegetable depend more on taste, culture, affordability etc. rather than on the dietary recommendations [1]. Australian adults get about 36% of their energy from energy-dense nutrient-poor foods (41% saturated fat and 47% sugar) [2]. High consumption of fat (60.7 g/day) and sugar (73.1 g/day) has been reported among Indians [3]. A mean salt intake of 12.5 g/day has been reported among 17 countries. Indians consume 10.98 g salt per day [4,5]. In parallel with high fat, sugar and salt consumption, low consumption of fruits and vegetables is common throughout the world. Only 5.6% Australians and 26% Indians meet WHO guidelines for fruits and vegetables (400 g/day) [6–8].

India is suffering from the double burden of malnutrition. More than 58.4% children, 53% women and 23% men are suffering from some form of anaemia. On the other hand, overweight and obesity increased by 8.1% in women and 9.3% in men between 2005 and 2016 [9]. Obesity is a major risk factor for chronic diseases such as cardiovascular diseases, diabetes, and certain cancers [10]. Most of these diseases can be prevented by changing diet and increasing physical activity [1].

Several interventions have been used to modify dietary and physical activity behaviours. Most of these interventions have targeted either diets or physical activity separately. Face-to-face individual counseling with an interpersonal component or group education sessions are common approaches [11]. Techniques that provide specific education tailored to individual needs have been more effective than generic nutrition education [12]. However, the high costs of such interventions make them impractical for population use [13]. As unhealthy diets are prevalent among the majority of people in most populations, nutrition interventions should reach a large number of people at low cost.

Web-based computer interventions present an alternative approach which allows individualized education in a cost-effective way [14]. Follow-up by email or phone has also shown encouraging results [15]. The use of mobile health applications continues to increase [16]. However, the effectiveness of information technology to improve dietary behaviours has not yet been established [17,18]. Since information technology tools are now widely available [19], we planned a cluster randomised controlled trial (CRCT) to test the effectiveness of an information technology-enabled nutrition education intervention called ‘SMART (Small, Measurable and Achievable dietary changes by Reducing fat, sugar and salt consumption and Trying different fruits and vegetables) Eating’. The objective of this paper is to describe the design and approach of the SMART Eating Trial.

## Methods

### Overview

The approach is based on the PRECEDE-PROCEED Model (Figure 1) [20]. Formative research was conducted to inform the development of the intervention (Supplementary file 1). A cluster randomised controlled trial (CRCT) design was employed to determine the effectiveness of the SMART Eating Intervention on an individual as well as at family level.

**Figure 1. F0001:**
[figure not shown]
PRECEDE-PROCEED Model (Green & Kreuter) [20].

### Study setting

A sector of Chandigarh city, located in northern India, has been chosen for the study. The selected sector has a population of about 30,000 and includes people of all socio-economic strata with the type of housing, assigned by the Chandigarh Administration as low-income group (LIG), middle-income group (MIG) and high-income group (HIG), taken as proxy for socio-economic status. This sector has been purposely selected because The Community Medicine Department of The Post Graduate Institute of Medical Education and Research (PGIMER), Chandigarh, has been working here to strengthen healthcare services, and use of mobile phones and internet is also widespread in this area.

About 89% households in Chandigarh use mobile or landline phones [21]. A rapid survey of the study area in 120 families from different types of housing during planning phase of the CRCT revealed that all families, including those from low-income group (LIG), had mobile phones. Most of these families had smart phones and internet services. India will have 450 to 465 million internet users in 2017 [22]. Mobile internet penetration is also high in India with 400 million internet users accessing the internet through mobile phones [23,24].

### Study design

A cluster-randomised controlled trial design with two groups will be employed: (1) The intervention group will receive community-led information technology-enabled SMART Eating Intervention. (2) The control group will receive traditional nutrition education through pamphlets (Figure 2). The objectives of the intervention are to: (a) Reduce the consumption of fat, sugar and salt by 20%; (b) Increase fruit and vegetable consumption by 20%; (c) Reduce the monthly purchase and consumption of fat, sugar and salt; (d) Increase the weekly purchase of fruits and vegetables; and (e) Identify barriers to dietary behaviour change and help families develop coping strategies.

**Figure 2. F0002:**
[figure not shown]
Study design.

### Sampling

A multi-level sampling strategy will be used. Twelve clusters, based on the type of housing (LIG, MIG and HIG), have been selected bearing in mind that there is sufficient geographic separation to avoid any spill-over effect of the intervention. Similar clusters will be paired together to form six pairs. For each of the six pairs, computer generated randomisation will be used to allocate clusters to intervention and control groups by a researcher not involved in the study. The number of clusters and cluster size will be fixed. Equal numbers of families will be recruited from each cluster through systematic random sampling. One adult (35–70 years) per family will be randomly selected as the index case for the baseline and post-intervention assessment.

One family champion (the adult member who cooks food most of the time) will be selected from each family for the implementation of the intervention. In recognition of the fact that not all family champions will be using information technology tools or mobile phones (as demonstrated through the formative research), one co-champion will also be selected from each family. A co-champion can be any person from the family identified by the family champion who would be able to assist him/her in using the internet and mobile phone communications.

### Inclusion and exclusion criteria

The inclusion criteria for recruitment of study participants will be: families from low, middle and high-income group housing (LIG, MIG, HIG); residing in the study area 6 months or more; having access to mobile phone/landline phone/internet; and including adults between 35 and 70 years of age. This age group has been selected because most of the youth (20–34 years) move away due to higher education and job opportunities etc. Moreover, adults between 35 and 70 years of age have higher chance of developing chronic diseases. Pregnant women and families not providing consent to participate in the study will be excluded.

### Sample size

Sample size calculations were done for each of the outcome variables: fat, salt, and fruit and vegetable intake, but not for sugar intake, because estimates of sugar intake were not available. The prevalence of adequate dietary intake for the different foods and nutrients was used to calculate the sample size for fat and fruit and vegetables based on dietary surveys and based on urinary salt excretion for salt. As no similar trials were available to inform an assumption of improvements in the intervention arm, the sample size was calculated based on a 20% improvement. Sample size for estimation of change in salt required the largest sample size. Based on a previous study, which indicated that 15% of adults had a salt intake of <5 gram per day [25], and assuming a 20% improvement in the intervention arm, power calculations (alpha = 0.80; p = 0.05) indicated that 83 participants would be needed per study arm. As the intra-cluster correlation co-efficient was not available for the outcome of interest, we used a design effect of 2, which increased the estimated sample size to 166 [26]. Taking into account a drop-out rate of 10%, we calculated that 183 participants would be required [27]. However, in order to enable comparison of outcomes between different age and socio-economic groups, the calculated sample size had to be doubled. Thus, a final sample size of 366 participants per study arm was deemed to be sufficient to assess changes in each of the study outcome.

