### Strengths and limitations

The main strength of this study is inclusion of all socio-economic groups in a sufficiently large representative sample with focus on all dietary components. Inclusion of all socio-economic groups will likely enhance the generalisability. The calculated sample size is large compared to other RCTs which should provide strong power. Strict randomisation throughout the sampling procedure will also help to minimise any potential bias although the lack of blinding will mean the results will have to be interpreted with caution.

Involvement of stakeholders in the formative research for intervention development is another strength of our study which draws on other studies [66]. The multi-channel communication approach for delivering the IT-enabled nutrition intervention is unique. Visitor count will be used as an indicator of use of website content by the participants, however, due to lack of resources we are not able to measure the time spent on the website. This study will provide important information on the feasibility, acceptability and effectiveness of multi-strategy intervention using information technology in bringing about dietary behaviour change in a developing country but it will not provide the comparative effectiveness of each component of the intervention.

Assessment of behaviour change is proposed at 6 months after the intervention. Ideally assessment should also be done 6 months after the active intervention to assess the maintenance of behaviours. However, due to resource constraints, we may not be able to continue beyond 6 months. Another limitation of our study is the selection of only one member from each family to measure dietary changes, as it is impractical to measure dietary intake of all members of the family. This may underestimate the effect size.

Access and use of IT by family champion can be a challenge, but a rapid survey of 120 families from different types of housing in the study area suggested high prevalence of IT use. Each family had at-least one mobile phone and majority had smart phones or computers with access to internet including those living in LIG housing. It is, therefore, assumed that this intervention which has made use of available IT tools will not pose additional burden on the families.

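### Doubling to 366 per arm inside 12 fixed clusters does not deliver the socio-economic comparisons that the Sample size section gives as its reason

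*Protocol article*

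**What the plan says.** The Sample size section of the protocol article starts from a survey in which "15% of adults had a salt intake of <5 gram per day" and goes on "assuming a 20% improvement in the intervention arm". It reports that "power calculations (alpha = 0.80; p = 0.05) indicated that 83 participants would be needed per study arm" (read here as 80% power at a 5% significance level). A design effect of 2, adopted because no ICC was available, gives 166 per arm. An allowance of 10% for drop-out gives 183. The last step is the one at issue: "in order to enable comparison of outcomes between different age and socio-economic groups, the calculated sample size had to be doubled", which gives 366 per arm.

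The Sampling section selects twelve clusters by low-, middle- and high-income housing, forms six pairs, randomises within pairs and takes equal numbers of families per cluster. It adds that "The number of clusters and cluster size will be fixed". The section on contextual factors influencing study design confirms that housing type stands in for socio-economic status. No power is given for any subgroup comparison. The Data analysis section plans regression to explore differences by socio-economic group, age and gender.

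**The concern.** A design effect depends on cluster size. If the number of clusters cannot grow, doubling the participants doubles the cluster size, so the design effect rises and part of the gain is lost. Socio-economic group is moreover a property of the whole cluster. A comparison within one housing type uses only that type's clusters, and there are three types, so a factor of two could not give each of them the size required for one comparison even without clustering.

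What is at stake is how the socio-economic results are read. If the published rationale says the trial was enlarged to make these comparisons possible, a non-significant result in one housing type, or no visible difference between types, is likely to be taken as evidence that effects are absent or equal.

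**Working it through.** **Inputs.** From the protocol: 15% baseline, 20% improvement, 80% power, 5% significance, design effect 2, 10% drop-out, doubling, 12 clusters (6 per arm), three housing types. Assumed: two-sided test; four clusters per housing type (two per arm), since the split is not stated; no gain from pairing or baseline adjustment.

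**1. The plan's own figure.** For 15% versus 35%:

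n₀ = [1.96√(2×0.25×0.75) + 0.8416√(0.1275+0.2275)]² / 0.2² = (1.200+0.501)²/0.04 ≈ 72.4

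With continuity correction: (n₀/4)[1+√(1+4/(0.2n₀))]² ≈ 82.1, rounded up to 83.

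Then 83×2 = 166, 166×1.1 ≈ 183 and 183×2 = 366. The chain reproduces. It does so only with 20 percentage points; a relative 20% (15% to 18%) would need about 2,400 per arm.

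**2. What doubling does to cluster size.** Recruited: 183/6 = 30.5, then 366/6 = 61. Analysed, on the plan's accounting: 166/6 = 27.7, then 332/6 = 55.3.

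**3. Information gained.** With DE = 1+(m−1)ICC, the ratio of effective sizes is [366/(1+60·ICC)] / [183/(1+29.5·ICC)]:
- ICC 0.01: 228.8/141.3 = 1.62
- ICC 0.0375: 112.6/86.9 = 1.30

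**4. Two readings of the design effect of 2.** No ICC is given, so both values are inferred:
- It belongs to the size at which it was applied, 27.7 analysed per cluster: ICC = 1/26.7 = 0.0375.
- It belongs to the final size of 61: ICC = 1/60 = 0.0167.

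**5. Within one housing type.** Analysed per arm: 332/3 = 110.7, in two clusters of 55.3. Effective n = 110.7/DE, SE = √(0.355/n_eff), normal power = Φ(0.20/SE − 1.96). The t version uses the noncentral t with 4−2 = 2 df.

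**6. Between two housing types (20 points in one, 0 in the other).** Variance = (0.1275+0.2275+0.1275+0.1275)/n_eff = 0.61/n_eff, with 8−4 = 4 df for the t version.

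| ICC | DE at 55.3 | n_eff per arm | Within: normal / 2 df | Between: normal / 4 df |
|---|---|---|---|---|
| 0.01 | 1.54 | 71.7 | 81% / 36% | 58% / 38% |
| 0.0167 | 1.91 | 58.1 | 72% / 31% | 50% / 32% |
| 0.0375 | 3.04 | 36.4 | 53% / 22% | 34% / 22% |
| 0.05 | 3.72 | 29.8 | 45% / 19% | 29% / 19% |

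Worked line at 0.0375: SE = √(0.355/36.4) = 0.0987; 0.20/0.0987 = 2.03; Φ(0.07) ≈ 53%.

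**7. Main comparison at ICC 0.0375.** n_eff = 332/3.04 = 109 per arm. Power for 15% to 35% is 94% (normal), 88% (10 df, unpaired clusters) or 80% (5 df, six pairs).

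**8. Age.** Age groups cut across clusters, so each half of a two-way split keeps all six clusters per arm at half the size. At ICC 0.0375, n_eff = 166/(1+26.7×0.0375) = 83 per arm, with power 86% (normal) or 79% (10 df).

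**The case against.** Several points on the other side stand.

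- The arithmetic from 83 to 366 is sound, and the ICC of 0.0375 is back-calculated from a cluster size the trial will not use. If the design effect of 2 was meant for 61 per cluster, no loss against the plan's own figure arises in the main comparison. It would therefore be wrong to state as fact that the doubled sample is worth 109 rather than 166 independent people per arm.
- The Data analysis section speaks of exploring group differences and states no confirmatory subgroup hypothesis, which already points towards the proposed labelling.
- The powers are somewhat pessimistic. Matching on housing type should remove some between-cluster variation, and baseline adjustment may help.

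Two stronger readings are tempting, and the document does not support them. A reader might infer that the whole trial is underpowered, so that calling 366 sufficient, or saying "The calculated sample size is large compared to other RCTs which should provide strong power", is wrong. Those statements concern the study outcomes and the trial in general, and the main salt contrast keeps 80–94% power at ICC 0.0375. A reader might also take the Background figure, "26% Indians meet WHO guidelines for fruits and vegetables (400 g/day", and conclude that "Sample size for estimation of change in salt required the largest sample size" is false, because 26% to 46% needs 99 per arm. But that figure refers to a WHO total. The NIN criterion under Primary outcome has two separate minimums, for fruit and for vegetables, and cannot be met more often than their 400 g sum in the same population. The survey prevalence actually used is not given. Below 15% the requirement would fall under 83 (71 at 10%), so no contradiction is shown.

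None of this rescues the stated reason for the doubling as far as socio-economic groups are concerned.

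**Conclusion.** The point holds for socio-economic comparisons only. With 12 fixed clusters defined by housing type, doubling gives each type about 111 analysed per arm in two clusters, two-thirds of the 166 required for one comparison. On either reading of the design effect, within-type power is below 80% (about 72% or 53%; 31% or 22% with 2 df), and a between-type contrast has about 50% or 34%. Only at an ICC near 0.01, and ignoring the few degrees of freedom, does within-type power reach about 80%; the between-type contrast is still 58% there.

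These figures rest on an even split of clusters over housing types, a 20-point effect, inferred ICCs and no credit for pairing or baseline adjustment. The main comparison meets its 80% target at the implied ICC, and the age rationale is roughly met for a two-way split. This is a size rationale that the design does not deliver. It calls for correction, but it changes neither the primary comparison nor the number recruited.

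**What to change.** 1. Justify 366 per arm (12 clusters of 61) by the main comparison between arms. Compute the design effect as 1+(m−1)ICC at the real cluster size, show power over a stated ICC range such as 0.01–0.05, and use cluster-level degrees of freedom (10 unpaired or 5 paired, to match the analysis).
2. Remove the statement that doubling enables comparison between socio-economic groups. If the age rationale is kept, say that it refers to a two-way split.
3. Label the socio-economic comparisons as exploratory and report them as arm-by-group interaction estimates with confidence intervals, not as separate significance tests within each housing type.

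The cost is a recalculation, some rewording and a less favourable stated justification. No participants or clusters are added.

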### Primary outcome

The primary outcome for the study is the % change in study participants meeting India’s National Institute of Nutrition (NIN) dietary guidelines for fat, sugar, salt, fruit and vegetable intake. The NIN recommend that, for adults, 20–30% energy should be from fat (10% from visible fat and 10–20% from foods other than visible fat); no more than 20 g sugar for women and 25 g sugar for men, less than 5 g salt, and at least 100 g of fruits and 300 g of vegetables per day.

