The existing literature shows that the diseases linked to high fat, sugar and salt intake, such as heart disease, diabetes, some cancers, and nutritional deficiencies, are preventable through increased consumption of fruits and vegetables [52–59]. Yet, many studies target one or two aspects of diet, few studies target multi-components of diet. The study conducted in rural South India [60] is an exception but also focused mainly on fruit and vegetable components; with fat, sugar and salt as the secondary outcome measures. The objective of the intervention here was therefore to focus on all the five dietary components together to develop a comprehensive health promotion intervention using IT.

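### The primary outcome is defined inconsistently (percentage meeting guidelines, or that plus change in intake), and for fat the two measures can move in opposite directions

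*Protocol article*

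**What the plan says.** Four places in the protocol article bear on the main result.

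- **Primary outcome** gives one binary measure per component: "The primary outcome for the study is the % change in study participants meeting" the national guidelines for fat, sugar, salt, fruit and vegetables. For fat the criterion is a range: "20–30% energy should be from fat".
- **Abstract** names that percentage as primary "and the change in intake of fat, sugar, salt, fruit and vegetables after the intervention". It adds that difference in differences will be applied to intakes.
- **Data analysis** computes both measures, but defines the net intervention effect (difference in differences) on intake only.
- **Sample size** works from the prevalence of adequate intake, which is the binary measure, for "fat, salt, and fruit and vegetable intake, but not for sugar intake". It concludes that 366 per arm is "sufficient to assess changes in each of the study outcome".

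Study design sets intervention objectives of a 20% reduction in fat, sugar and salt and a 20% increase in fruit and vegetables. Secondary outcomes lists body measurements, blood tests and urinary salt. Dietary intake is not on that list.

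**The concern.** Change in intake is primary in the Abstract, absent from the Methods definition of the primary outcome, not listed as secondary, and the headline effect in Data analysis. A reader cannot tell whether the trial's question is answered by five percentages or by five percentages and five changes in intake. No component leads, and no composite of meeting all five is defined.

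Two things are at stake. First, Data collection says that neither the investigator nor the data collectors are blinded, so an unsettled definition leaves room to choose the favourable version once results are visible. Second, the two versions are not interchangeable for fat. A band criterion is compared with a one-directional aim, so the same change in diet can be a success on one measure and a failure on the other.

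**Working it through.** **1. What the sample size was built on.** Inputs from Sample size: 15% with adequate salt intake, a 20% improvement, p = 0.05, and 0.80 (labelled alpha, read here as power). The stated 83 reproduces only if 20% means percentage points, 15% to 35%.

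n = [1.96·√(2·0.25·0.75) + 0.842·√(0.15·0.85 + 0.35·0.65)]² / 0.20² = 72.4

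With continuity correction: (72.4/4)·[1 + √(1 + 4/(72.4·0.20))]² = 82.1, rounded up to 83.

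Then 83 × 2 = 166, 166 × 1.10 = 183, and 183 × 2 = 366. The figure is for one binary endpoint at two-sided 0.05, with no allowance for several endpoints.

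**2. Counting endpoints.** The Discussion speaks of a "focus on all the five dietary components together".

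| Place | Binary | Change in intake | Primary results |
|---|---|---|---|
| Primary outcome | 5 | not named | 5 |
| Abstract | 5 | 5 | 10 |
| Data analysis | computed | computed, carries the net effect | not stated |

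**3. Fat: can the two measures disagree?** Let baseline fat, as a share of energy, be normal with mean μ and SD σ (assumed). The share inside the band is

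P = Φ((30 − μ)/σ) − Φ((20 − μ)/σ).

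A uniform 20% cut with energy unchanged (assumed) replaces μ and σ by 0.8μ and 0.8σ.

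| μ, % of energy | SD 5: before → after | SD 7: before → after |
|---|---|---|
| 24 | 67% → 42% | 52% → 42% |
| 27 | 64% → 64% | 51% → 55% |
| 30 | 48% → 77% | 42% → 62% |

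The sign changes at μ = 27.1 for SD 5 and 26.3 for SD 7. If the lost energy is not replaced, it changes at 26.5 and 26.0.

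The only fat level in the document is 60.7 g/day for Indians (Background). At 9 kcal/g, 60.7 × 9 = 546 kcal. That is 30.4%, 27.3%, 24.8% or 22.8% of energy at an assumed 1,800, 2,000, 2,200 or 2,400 kcal. Between the two ends of that range the change in the share inside the band runs from +33 to −31 points (SD 5) or from +21 to −15 points (SD 7).

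**4. False-positive chance, conditional.** Suppose every null hypothesis is true, each test is two-sided at 0.05, and any one significant result is called success.

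- Five independent tests: 1 − 0.95⁵ = 22.6%.
- Five tests with common correlation 0.3, 0.5 or 0.7 (simulated): 20.8%, 18.3%, 14.9%.
- Ten independent tests: 1 − 0.95¹⁰ = 40.1%. This is only a ceiling, because the binary and continuous versions of a component come from the same questionnaire values.
- Ten tests as five pairs, within-pair correlation 0.5 to 0.9 and between-component correlation 0 to 0.5 (simulated): about 38% down to 25%.

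**5. Power at the strictest Holm step.** For five endpoints this is 0.05/5 = 0.01. With 10% dropout and design effect 2, effective n per arm is 366 × 0.9/2 = 165. The standard error for 15% against 35% is √[(0.1275 + 0.2275)/165] = 0.0464, so the noncentrality is 0.20/0.0464 = 4.31. Noncentral t, with degrees of freedom from the 12 clusters:

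| Level | 10 df (unpaired) | 5 df (six pairs) |
|---|---|---|
| 0.05 | 97% | 93% |
| 0.01 | 84% | 63% |

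At an effective n of 109, taken as a pessimistic case (a larger design effect, assumed), power at 0.01 is 64% and 43%.

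**The case against.** The strongest reply is that this is a condensed article and an analysis plan may exist. Multiplicity procedures and success rules are commonly left to such a plan, so their absence here is not a fault. That stands. It does not cover the disagreement between the Abstract and the Primary outcome section, which is printed and which an analysis plan would have to resolve.

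A reader might infer that each endpoint is tested at 5% and that the trial carries an 18–40% chance of a false claim. The document does not support this. The 0.05 level appears once, in "power calculations (alpha = 0.80; p = 0.05) indicated that 83 participants would be needed per study arm", which concerns salt, and Data analysis states no level. Nothing says that one significant result is enough. The 40% end needs ten independent tests, which paired endpoints from one questionnaire cannot be.

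A reader might also infer that the fat result will reverse. The 60.7 g/day is a background figure, no baseline distribution is given, and at an assumed 2,000 kcal the share in the band still rises slightly (+2.5 points at SD 5, +5.5 at SD 7). It is also fair to say that a guideline-adherence endpoint is meant to exclude people below the lower limit. What stands is that the reversal is possible at plausible levels, and that the fat criterion and the fat objective are not aligned.

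Finally, Study design lists objectives of the intervention, not trial endpoints, so it does not show that intake ought to be the primary measure.

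**Conclusion.** The point holds as an inconsistency in the definition of the primary outcome and needs correcting. Its core rests on the text alone: five primary results in one place, ten in another, and the net effect attached to the measure that the Methods definition leaves out.

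The fat conflict is conditional. Under the normal model with a uniform 20% cut and unchanged energy, a successful reduction lowers the share meeting the guideline when mean baseline fat is below about 26–27% of energy. Above that level the two measures agree.

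The false-positive range is illustrative: about 15–23% for five endpoints and 25–38% for ten. It depends on the assumed correlations and on a success rule that the document does not state, so it should not be quoted as a property of the trial.

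**What to change.** State one primary family in the same words in the Abstract, Primary outcome and Data analysis. The least change is to keep the percentages meeting the guidelines as primary, since the sample size rests on them, and to list change in intake as secondary. Making intake primary instead would be a preference and would demote the endpoint on which the trial was sized.

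Say what counts as success across the five components. If a claim may rest on any one of them, use Holm at a family-wise 5%.

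Reconcile the fat band with the fat objective. Report the shares above 30% and below 20% of energy separately, next to mean fat intake, so that an intended reduction is not read as failure.

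Most of this costs only wording. Holm is the exception. With 12 clusters, moving from 0.05 to 0.01 takes power for 15% to 35% from about 97% to 84% in an unpaired analysis, and from about 93% to 63% if the six pairs are kept in the analysis (effective n 165). A normal approximation would hide this loss. If that cost is too high, one lead component or a stated rule requiring success on all five avoids the adjustment, although the second has its own power cost.
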